## Figures and Tables

**Figure 1 life-15-00168-f001:**
[figure not shown]
Schematic view of the study protocol timeline. Full arrows represent defined duration (i.e., 12 weeks for aPL confirmation assay, or 6 weeks for AVF maturation evaluation), and dotted arrows represent undefined periods.

**Figure 2 life-15-00168-f002:**
[figure not shown]
Pathophysiological hypothesis of aPL-associated AVF maturation failure. The first line represents the pathways implicated in the pathophysiology of APS and the second line represents the presentation of AVF maturation failure (either in the presence of thrombosis, stenosis or because of insufficient venous remodeling). The dashed arrows represent pathophysiological hypotheses that have not been studied in the literature, while the solid arrows represent associations described in the literature. MCP-1: Monocyte Chemotactic Protein 1, MMP: matrix metalloproteases, mTOR: mammalian Target of Rapamycin, NO: nitric oxide, TIMP-1: tissue inhibitor of metallo-proteinase-1.

**Table 1 life-15-00168-t001:** Baseline characteristics collected at the time of AVF surgical creation.

Parameters	
Demographics	Age
	Gender
	BMI (kg/m^2^)
	Ethnicity
	Smoking status
Treatments	Anti-platelet therapy
	ACE/ARBs
	Statins
	Erythropoietin
	Anticoagulation therapy
	Beta-blockers
Medical history	Etiology of CKD, histologically proven
	Diabetes mellitus
	Hypertension
	Coronary heart disease
	Stroke or TIA
	Ischemic heart disease
	Peripheral vascular disease
	Left ventricular ejection fraction
	Deep vein thrombosis (n, %)
	Other aPL related clinical features
Biological	Hemoglobin level
features	Platelet count, mean platelet volume
	Coagulation tests: activated PTT, fibrinogen, Prothrombine time
	Lipids
	c-reactive protein, ESR
	Nt-proBNP
Vascular access	Need for catheter before AVF use
parameters	AVF creation date, AVF type, surgical procedure information (type of anesthesia, artery and vein diameter, anastomosis diameter)
	Mapping details
	Perioperative complications: bleeding, local hematoma, other complications
	Pre-operative Flow mediated dilation of the brachial artery as a marker of endothelial dysfunction

ACE: angiotensin-converting enzyme inhibitors; ARB: angiotensin II receptor blockers; AVF: arteriovenous fistula; BMI: body mass index; CRP: c-reactive protein; TIA: transient ischemic attack.

**Table 2 life-15-00168-t002:** Primary and secondary outcomes.

Primary Outcomes	
AVF maturation	Defined 6 weeks after AVF creation, by US: AVF brachial artery blood flow > 600 mL/min, outflow vein diameter > 6 mm;
	Defined clinically if cannulation is possible with two needles for at least 75% of HD sessions over a continuous 4-week period, including either a mean HD machine blood pump speed superior to 300 mL/min over four consecutive sessions or a measured urea Kt/V > 1.4, or a urea reduction ratio (URR) > 70%
Assisted maturation	Need for any intervention (e.g., ballon angiography, etc.) in order to promote maturation
Time to first AVF puncture	

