Although ESKD is rare in APS, the prevalence of persistent aPL positivity is higher in HD patients compared to the general population, and can reach more than 35% [8]. The reason for such a high prevalence of aPL positivity in HD is not well known. Several hypotheses have been proposed such as (a) molecular mimicry as a response to the exposure to microorganisms, endotoxins or HD membranes, or (b) a response to oxidation (i.e., cross-reactive immunoglobulins against epitopes of oxidized lipids) [8]. Nevertheless, aPL positivity has been inconsistently associated with AVF thrombosis [8,9,10,11]. Also, aPL positivity has been rarely associated with AVF stenosis [12] and intrastent restenosis [13]. Recently, our group published the first report of a significant association between aPL persistent positivity, and native AVF maturation failure as defined by US in a retrospective study including 116 HD patients [14]. The aPL positivity was a strong predictor of AVF maturation failure in multivariate analysis.

The aim of the present study is to confirm this association in a prospective cohort. The primary outcome of the study is to examine the possibly causative link between aPL persistent positivity and the occurrence of AVF maturation failure defined by the clinical approach combined with US.

Secondary outcomes will focus on clinical outcomes other than AVF maturation: functional primary patency and primary patency, time to AVF complications, AVF thrombosis or stenosis rates, bleeding complications rates and HD adequacy parameters.

In addition, in order to better understand the underlying pathophysiological mechanism of AVF maturation failure in aPL positive patients, we will perform blood analyses as well as an in vitro study using cultured immortalized human microvascular endothelial cells type 1 (HMEC-1).

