### 2.2. Participants

Patients are eligible for inclusion if they fulfill the following criteria: patients with chronic kidney disease (CKD) on stage G3b to G5 who have not yet started HD, aged from 18 to 75 years old, who are planned for a first native AVF surgical creation as decided by a multidisciplinary team comprising nephrologists and vascular surgeons, irrespective of previous aPL status.

Exclusion criteria are the following: ESKD patients switching from peritoneal dialysis to HD, AVF creation not feasible surgically or technically, endovascular AVF, innate or acquired thrombophilia other than APS, active neoplasia, aPL assays not relevant (because of anti-vitamin K treatment, inflammatory state, absence of confirmation assay, etc.).

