### 2.4. Follow Up

Participants will be followed clinically for 1 year after the date of AVF creation (Figure 1. Study protocol).

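### Clinical maturation and time to first puncture are primary outcomes that can be observed only on haemodialysis, but the cohort is pre-dialysis and need not start within the one-year follow-up

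*Protocol article*

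**What the plan says.** Section 2.2 admits "patients with chronic kidney disease (CKD) on stage G3b to G5 who have not yet started HD", provided a multidisciplinary team has planned a first native fistula. No criterion requires HD to be expected within a given time. Section 2.4 sets the clock: "Participants will be followed clinically for 1 year after the date of AVF creation".

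Under Primary Outcomes, Table 2 gives two definitions of maturation.

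- **Ultrasound:** "Defined 6 weeks after AVF creation, by US: AVF brachial artery blood flow > 600 mL/min, outflow vein diameter > 6 mm".
- **Clinical:** "Defined clinically if cannulation is possible with two needles for at least 75% of HD sessions over a continuous 4-week period", with in addition a "mean HD machine blood pump speed superior to 300 mL/min over four consecutive sessions or a measured urea Kt/V > 1.4", or a URR above 70%.

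The same block lists "Time to first AVF puncture" with no time origin and no condition on HD start. The Introduction states the primary outcome as the "occurrence of AVF maturation failure defined by the clinical approach combined with US".

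Section 2.8 says that all available data will be used, and plans Kaplan–Meier estimates for primary patency and functional primary patency only.

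**The concern.** Each part of the clinical definition is a measurement taken during HD sessions, yet nobody is on HD at entry and some may not be on it a year later. For those patients the criterion says nothing about the fistula. Calling them not matured records false failures; leaving them out makes the analysis conditional on having started dialysis. Time to first puncture has the same difficulty, because an excellent fistula in a slowly progressing patient is punctured late.

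The study is meant to confirm an association, to examine a possibly causative link and, according to the Discussion, perhaps to support routine aPL screening. A primary outcome that mixes vein remodelling with the timing of dialysis weakens each of these aims.

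**Working it through.** **Step 1. Set the definitions against the cohort.**

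| Outcome (Table 2) | Requires HD? | Time fixed in the article |
|---|---|---|
| US maturation | No | 6 weeks after creation |
| Clinical maturation | Yes, a 4-week run of sessions | None stated |
| Time to first puncture | Yes, in practice | No origin stated |

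One year is about 52 weeks and the run takes 4, so HD through the fistula must begin by about week 52 − 4 = 48. Anyone starting later, or not at all, cannot meet the clinical definition whatever the state of the fistula.

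**Step 2. The plan's own figure.** Section 2.1 gives 96 patients for 50% versus 70% failure, two-sided alpha 0.05 and 90% power. The pooled two-proportion formula gives 124 per group (248 in total). With 100 patients, power is 53% at 1:1 and 49% at 35:65. That is a separate defect. It matters here only because the losses below start from 49%, not from 90%.

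**Step 3. Inputs for the scenarios.**

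- N = 100, and failure of 50% and 70% (section 2.1).
- Split 35:65, an illustrative assumption. The Introduction says prevalence can exceed 35%, but in HD patients, not in this pre-HD cohort.
- Share f starting HD in time to be assessed: not in the article; assumed to be 40 to 80%, and equal in both groups.
- Failure among starters is taken as the planned 50% and 70%.

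Power = Φ[(d − 1.96·SE₀)/SE₁], where d is the difference in failure rates, SE₀ uses the pooled rate and SE₁ the separate rates.

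Example at f = 1 (65 controls, 35 aPL positive): pooled rate = 0.65×0.50 + 0.35×0.70 = 0.57; SE₀ = √[0.57×0.43×(1/65 + 1/35)] = 0.1038; SE₁ = √[0.25/65 + 0.21/35] = 0.0992; power = Φ[(0.20 − 0.2034)/0.0992] = Φ(−0.03) = 49%.

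**Step 4. Two ways of handling non-starters.** If they are excluded, the group sizes become 65f and 35f. If they count as failures, the rates become 1 − 0.5f (control) and 1 − 0.3f (aPL positive) with all 100 kept.

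| f | Assessable | Power, starters only | Rates if non-starters fail | Difference | Power |
|---|---|---|---|---|---|
| 1.0 | 100 | 49% | 50 vs 70% | 20 points | 49% |
| 0.8 | 80 | 40% | 60 vs 76% | 16 points | 35% |
| 0.6 | 60 | 31% | 70 vs 82% | 12 points | 24% |
| 0.4 | 40 | 22% | 80 vs 88% | 8 points | 16% |

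A 1:1 split shows the same pattern: 53, 45, 35 and 25% for starters only, and 53, 40, 29 and 19% with non-starters as failures.

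**Step 5. When does bias between groups arise?** Suppose aPL has no effect (50% failure among starters in both groups) and non-starters count as failures. With HD start of 80% in controls and 60% in aPL positive patients, apparent failure is 1 − 0.8×0.5 = 60% versus 1 − 0.6×0.5 = 70%: a 10-point difference from dialysis timing alone. Swapping the start rates reverses the sign. With equal start rates the difference is zero.

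**The case against.** The strongest reply is that the article never says what happens to patients who do not reach HD, and a full protocol or SAP, not shown here, commonly settles such handling. That is fair as regards the analysis rule: a reader might infer that non-starters will be counted as failures, but nothing says so, and the power figures are scenarios. It does not remove the point, because no analysis rule can make a criterion built on HD sessions observable in a patient who is not on HD. Population, endpoint and follow-up clock are all fixed in the article.

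Several stronger readings are tempting and should be resisted.

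- **A 6-week limit on clinical maturation.** The Figure 1 legend mentions "or 6 weeks for AVF maturation evaluation", which might suggest that cannulation must begin by week 2. In Table 2 the 6 weeks belong to the US definition; the clinical definition carries no such limit, and the legend also allows for undefined periods.
- **Time to puncture as mainly a measure of renal decline.** No figure supports this. Patients are not an unselected G3b population, since a fistula has already been planned. The time to puncture contains the wait for dialysis; how much is unknown.
- **The whole primary analysis is compromised.** Combining the clinical approach with US need not mean a composite; the Abstract speaks of evaluation clinically and by ultrasound. The US outcome stands by itself.
- **The sample-size rates are affected.** Section 2.1 does not say which definition the 50% and 70% refer to. The earlier retrospective study defined failure by US. If the rates are US-based, the power losses above do not apply to them.

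Two objections concern the remedy, and both stand in part. Restricting clinical maturation to HD starters keeps some selection on dialysis start. Also, the Discussion wants clinical as well as US follow-up because the earlier US finding might be an artefact of combining two measures, so the clinical endpoint should be kept.

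**Conclusion.** The point holds. Two outcomes listed as primary cannot be observed, or are partly driven by the timing of dialysis, in a cohort enrolled before HD and followed for one year from fistula creation. The 6-week US outcome is not affected.

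The size depends on an HD-start share that the article does not give. Under the stated assumptions, power for the clinical comparison falls from 49% to 22–40% among starters, or to 16–35% with non-starters as failures, provided the planned rates refer to the clinical endpoint. A reader might infer that the aPL comparison is biased. The documents do not show that: it would require HD start to differ by aPL status, for which they give no evidence. Without such a difference the harm is a diluted contrast or fewer assessable patients.

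**What to change.** - Name 6-week US maturation, which does not depend on dialysis and can be measured in every patient, as the endpoint for the confirmatory comparison.
- Keep clinical maturation as a key supportive endpoint in patients who start HD, over a fixed window from the later of HD start and a stated minimum time after fistula creation.
- Classify patients without enough HD time as not assessable, never as failures. Report their number and the HD-start rate by aPL group.
- State that the HD-starter analysis is conditional on dialysis start.
- Report time to first puncture among HD starters from the later of fistula creation and HD start, alongside the time from creation. The first removes the wait for dialysis; the second keeps visible any slow maturation that was over before HD began.

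No new clinical measurements are needed, though the date of HD start must be available for each patient. The cost is that clinical maturation becomes supportive with a smaller denominator, and the endpoint hierarchy of a registered study that began in August 2023 must be amended.

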**Secondary outcomes**	
Primary patency rate	Defined as the time period from AVF creation to the first intervention in order to maintain AVF patency
Functional primary patency rate	Defined as the time period from AVF first cannulation to intervention in order to maintain AVF patency
Thrombosis	Defined as any acute change in AVF physical examination of blood flow leading to a complete inability to perform dialysis.
Stenosis	Defined as chronic change in AVF physical examination of blood flow, associated with a confirmation by using either US or angiography (stenosis of more than 50% in diameter).
Bleeding complications	
HD adequacy	Defined by the Urea Kt/V and Urea Reduction ratio (URR)

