## 2. Materials and Methods

### 2.1. Design and Objectives

This is a monocentric observational prospective cohort study that aims to recruit a cohort of 100 newly created native AVF in CKD patients with a previous aPL profile determination before AVF creation and HD initiation.

The sample size calculation was based on the assumption that the expected maturation failure rate in the general population is 50%, and is 70% in the aPL positive group. With alpha = 0.05, 1-Beta = 90%, and a two-sided test, 96 patients are required to detect a significant difference. Thus, we plan to enroll and analyze 100 patients.

Surgical AVF creation is performed as per standard of care without procedural variations between the aPL+ and control groups, ensuring homogeneity in the approach. No perioperative treatments or clinical assessments are specified by the study protocol.

Institutional Review Board authorization was obtained from the Brugmann University Hospital Ethics Committee (Reference number: CE2022/113), in accordance with the Declaration of Helsinki. Written informed consent is obtained from patients before any inclusion procedure. This study was registered on ClinicalTrials.gov (ID number: NCT06112821), and the study was started on August 2023. The study protocol is illustrated in Figure 1.

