### 2.8. Statistical Analyses

The total expected sample size is assumed to be a minimum of 100 patients based on an average recruitment rate of 2 patients/month. Analyses will describe AVF clinical outcomes for patients with and without persistent aPL positivity, potential predictors of patient outcome. Analyses will use all available data, regardless of final sample size.

Data will be expressed as mean ± standard deviation (SD) for variables with a normal distribution or as median ± interquartile range (P25; P75). Student’s t-test will be used to compare the means of the quantitative variables following a normal distribution by group. The Mann–Whitney Wilcoxon test will be used to study the variation between two groups of variables following an asymmetric distribution. The significance level of the tests was 0.05 with odds ratios and 95% confidence intervals. Multivariate models will be performed through logistic regression for variables showing statistically significant differences between groups.

We will employ Kaplan–Meier survival analysis to estimate the probability of AVF primary patency and functional primary patency over time.

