## 3. Discussion

AVF maturation failure is a frequent complication that occurs in more than half of cases after surgical creation of the AVF, and often requires the use of intervention [16], possibly leading to significant morbidity and mortality [1,2,16]. Therefore, a better understanding of the risk factors of AVF maturation failure is of importance in order to identify prophylactic or therapeutic strategies.

In the setting of persistent aPL positivity, AVF maturation failure could be related to early AVF thrombosis. Also, APS has been associated with endothelial dysfunction and intimal hyperplasia with stenotic lesions in some aPL-related manifestations such as APS nephropathy [17,18]. We recently described the association between aPL persistent positivity, and native AVF maturation failure defined by US. aPL positivity was a strong predictor in multivariate analysis; however, this association was independent of AVF stenosis or thrombosis during the maturation process [14]. These findings might suggest that aPL persistent positivity could be responsible for the inability of the efferent vein vasodilatation and remodeling leading to AVF maturation failure. However, these findings might also reflect the statistical artifact of combining two outcomes (i.e., AVF rachial artery blood flow and outflow vein diameter). Therefore, in order to confirm these results, we propose a prospective observational cohort study that aims to recruit a cohort of newly created native AVFs with a previous aPL determination and 12-week confirmation assays, with longitudinal clinical and US follow-ups. Analyses will describe AVF clinical outcomes, in terms of maturation, in patients with and without persistent aPL positivity, potential predictors of patient outcome. The results could have a significant clinical impact and pave the way for new exploratory or confirmatory studies.

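### Both patency outcomes end only at an intervention, so a fistula that thromboses or is abandoned without one is never counted as having lost patency

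*Protocol article*

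**What the plan says.** Table 2 of the protocol article, under secondary outcomes, gives primary patency as "Defined as the time period from AVF creation to the first intervention in order to maintain AVF patency" and functional primary patency as "Defined as the time period from AVF first cannulation to intervention in order to maintain AVF patency". The two differ in when the clock starts. They share a single end event, an intervention.

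Thrombosis is a separate row: "Defined as any acute change in AVF physical examination of blood flow leading to a complete inability to perform dialysis". Nothing links it to the patency rows. Abandonment of a fistula is not mentioned in Table 1, in Table 2 or in the text.

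Section 2.8 states the method: "We will employ Kaplan–Meier survival analysis to estimate the probability of AVF primary patency and functional primary patency over time". It adds no further end event. Section 2.4 sets the horizon: "Participants will be followed clinically for 1 year after the date of AVF creation". Section 2.3 adds that patency will also be explored in the two aPL positive subgroups, APS and carriers.

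**The concern.** Patency analysis should show how long a fistula stays open without help. An intervention is one way for that period to end. The others are that the fistula clots and is not rescued, or that it is given up in favour of another access. Under the Table 2 wording these have no event date, although they are the worst results a fistula can have.

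If untreated loss were equally common in both groups, patency would be overstated to a similar degree in each. The article gives a reason to expect a difference. Its Discussion says: "In the setting of persistent aPL positivity, AVF maturation failure could be related to early AVF thrombosis". If that is right, the uncounted losses fall more heavily on the aPL positive group, and the patency comparison is distorted towards no difference. At stake is whether the two patency curves, overall and by subgroup, can be read as descriptions of fistula survival.

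**Working it through.** The article states no patency rate, event count or power for these outcomes, so there is no figure to reproduce. The check has two parts: what the rule does to each kind of fistula, and how far the estimate could move under assumed rates.

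**Part 1. Applying the rule**

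| Course of the fistula | Event under Table 2? |
|---|---|
| Open for one year, no intervention | No (correct) |
| Stenosis, treated to maintain patency | Yes |
| Thrombosis, then declotted or revised | Yes, at the intervention date, if restoring patency is read as maintaining it |
| Thrombosis, no intervention | No |
| Abandoned, no intervention | No |

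The last two rows are the problem. In a Kaplan-Meier analysis they can only be censored at loss or kept at risk, event-free, to one year.

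**Part 2a. Simple illustration (all rates assumed)**

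Of all fistulas created, 20% have an intervention in each group. Loss without intervention is 20% in aPL positive and 5% in aPL negative patients.

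- Intervention and untreated loss both counted: 1 − 0.20 − 0.20 = 0.60, and 1 − 0.20 − 0.05 = 0.75. The difference is 15 points.
- As written, losses kept event-free: 1 − 0.20 = 0.80 in both groups. The difference is 0.
- As written, losses censored before any intervention occurs: 1 − 0.20/0.80 = 0.75, and 1 − 0.20/0.95 = 0.79. The difference is about 4 points.

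The overstatement is 15 to 20 points in the aPL positive group and 4 to 5 points in the aPL negative group.

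**Part 2b. Constant hazards over one year (all rates assumed)**

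Here 30% is the one-year risk of intervention acting alone, the same in both groups: h = −ln(0.70). Untreated loss acting alone has risk a, with hazard g = −ln(1 − a).

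- As written, losses censored: exp(−h) = 70.0%.
- As written, losses kept at risk: 1 − [h/(h + g)] × [1 − exp(−(h + g))].
- Both end events counted: exp(−(h + g)), with hazard ratio (h + g₁)/(h + g₀), where 1 is aPL positive and 0 is aPL negative.

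| a, negative vs positive | Censored | Kept at risk | Both counted | Hazard ratio, both counted |
|---|---|---|---|---|
| 5% vs 15% | 70.0% vs 70.0% | 70.7% vs 72.2% | 66.5% vs 59.5% | 1.27 |
| 10% vs 20% | 70.0% vs 70.0% | 71.4% vs 72.9% | 63.0% vs 56.0% | 1.25 |
| 10% vs 30% | 70.0% vs 70.0% | 71.4% vs 74.5% | 63.0% vs 49.0% | 1.54 |

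Under censoring, the hazard ratio as written is 1.00 in every row. The overstatement runs from 3.5 points (70.0 − 66.5) to 8.4 points (71.4 − 63.0) in the aPL negative group, and from 10.5 points (70.0 − 59.5) to 25.5 points (74.5 − 49.0) in the aPL positive group.

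The two illustrations differ under censoring because 2a fixes the observed share with an intervention and places every loss early, while 2b fixes the underlying risk and spreads losses over the year. Both give estimates that are too high, and more so where more fistulas are lost untreated.

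**The case against.** The strongest reply is that the article is condensed. It states no rule for censoring or competing events, and such rules commonly sit in a fuller document. That stands in part: how an abandoned fistula would be coded is not shown, so the size of the distortion is conditional. The end event itself, however, is stated, and neither way of coding such a fistula within that definition makes it a loss of patency.

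A second reply is that outright loss is seen elsewhere. This also stands. Maturation failure is the primary outcome, thrombosis has its own row, and the Introduction lists "functional primary patency and primary patency, time to AVF complications, AVF thrombosis or stenosis rates, bleeding complications rates and HD adequacy parameters". A reader might infer that the definition hides the effect under study. The documents do not support that, because the main hypothesis is tested on maturation. The separate rows do not, however, correct the two patency curves. The thrombosis row also has a limit of its own: it requires that dialysis cannot be performed, while section 2.2 admits only patients who have not started HD, so clotting before HD may not clearly qualify.

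A reader might also infer that the aPL positive group must look as good as the controls or better. The early-censoring case (75% versus 79%) shows otherwise, and the exact ties in the working come from assuming equal intervention rates.

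Finally, a reader might turn the sample-size assumption in section 2.1 ("expected maturation failure rate in the general population is 50%, and is 70% in the aPL positive group") into counts of fistulas that would enter functional patency. That would need a group split the article does not give. It would also treat every maturation failure as never cannulated, whereas Table 2 allows for assisted maturation and starts this clock at first cannulation.

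**Conclusion.** The point holds for both patency outcomes. With intervention as the only end event, fistulas lost without one are censored or counted as patent, and estimated patency is too high. The excess is larger in whichever group has more untreated losses. The article's early-thrombosis hypothesis makes the aPL positive group the plausible one, but the article does not establish this.

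The size cannot be taken from the document. Under the assumed rates, a 15-point difference shrinks to between 0 and 4 points, or a hazard ratio of 1.25 to 1.54 becomes 1.00. If losses are kept at risk, the order of the groups can reverse slightly. These results rest on equal intervention rates and on more untreated loss in aPL positive patients.

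The harm is limited to secondary estimates, so the definitions should be corrected, but the primary question is untouched.

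**What to change.** In Table 2, define loss of patency for both outcomes as the earliest of:

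- an intervention to maintain or restore patency;
- thrombosis, stated to include clotting before HD starts;
- abandonment of the fistula.

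Keep the present starting points: creation for primary patency and first cannulation for functional primary patency. Censor fistulas that are still patent at end of follow-up, death, transplantation, withdrawal or loss to follow-up, and say so.

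The cost is two revised definitions and possibly one new data field, since a date of abandonment is not among the items listed in Table 1 or Table 2. Reported patency will be somewhat lower. Patient care does not change.
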